### Implementation outcomes and determinants

2.7

Implementation outcomes and determinants will be assessed among patients and healthcare professionals in the intervention group only, guided by the Theoretical Domains Framework (TDF), the Consolidated Framework for Implementation Research (CFIR), the theoretical framework of acceptability (TFA), and Proctor et al.’s conceptual model [[55], [56], [57]]. Quantitative and qualitative methods will be used, as detailed in Table 2.

**Table 2 tbl2:** Implementation outcomes.

Outcome	Data Source	Timeline	Framework
Healthcare professionals			
Acceptability Appropriateness Feasibility	Acceptability of Intervention Measure (AIM) Questionnaire Intervention Appropriateness Measure (IAM) Questionnaire Feasibility of Intervention Measure (FIM) Questionnaire	GPs (IG) & PTs: At the end of training, after patient recruitment. OTs: After patient recruitment only	Proctor
	Focus Group with GPs, PTs and OTs	After patient recruitment	TFA, Proctor
Adoption *Proportion of recruited patients managed according to PRIME by GPs*	Patient self-report in REDCap and data from healthcare insurances: 1. Alignment of GP decision with treatment pathway recommendation 2. Rate of imaging and medication prescription 3. Work absence prescription 4. Rate of booklet use: “Did your doctor used resources (information booklet, website, drawings, …) to explain my low back pain during the last consultation? *Response: yes/no + free text to describe it*	1-3. Over the recruitment period 4. Baseline 2	Proctor
	Focus Group with GPs	After patient recruitment	Proctor
Adoption *Proportion of patients having physiotherapy sessions managed according to PRIME by PTs*	Patient self-report in REDCap: • Did the patient see a trained PRIME PT? PT checklist: • To what extent did you use the PRIME intervention with this person? *Response: 0: Not at all; 1: A little; 2: Moderately; 3: A lot (Adoption considered for 2 or 3 points)*	Over the recruitment period	
	Focus Group with PTs	After patient recruitment	Proctor
Fidelity - GPs *The degree to which the intervention is delivered as intended.*	GPs: Indirect measure through patient self-report in REDCap: 1. Reassurance: To what extent did the physician … - Reassure you that he/she had no serious concerns about your back - Explain how the treatment offered would help with your problem *Response: 0 (Not at all) - 6 (Extremely). > 3 was considered as fidelity* 2. LBP beliefs and Fear avoidance - Back-PAQ score - FABQ score	Baseline 2	Proctor
	Focus Group with GPs	After patient recruitment	Proctor
Fidelity - PTs *The degree to which the intervention is delivered as intended.*	PT checklist • To what extent did you explore beliefs (using reflections, open-ended questions, etc.)? • To what extent did you explore problematic functional movements? • To what extent did you modify movement, increasing muscle relaxation, speed, and amplitude ? • To what extent did you expose the person to functional movements that were feared and/or painful for them? • To what extent did you use load and speed in the exercises? • To what extent did you use a variety of exercises during the sessions ? • To what extent did you use explanations to reassure the person that were centered on their history and physical examination? • To what extent did you discuss returning to activities, using pacing and the gradual increase of physical activities? • To what extent did you propose strategies for managing new episodes/flare-up ? *Response: 0: Not at all; 1: A little; 2: Moderately; 3: A lot (Fidelity considered for 2 or 3 points)*	At the end of physiotherapy treatment sessions	Proctor
	Focus Group with PTs	After patient recruitment	Proctor
Perception of biopsychosocial competencies amongst PTs	Semi-structured interviews	After training	TDF; CFIR
Barriers and Facilitators of PRIME in clinical practice	Semi-structured interviews with PTs	After training	TDF; CFIR
	Focus group with GPs, PTs and OTs	After patient recruitment	

Patients			
Acceptability and experience	Satisfaction with the intervention, collected through patient self-report in REDCap: • To what extent were you satisfied with the care provided by your general practitioner for your back pain? • To what extent were you satisfied with the care provided by your physiotherapist for your back pain? • To what extent were you satisfied with the care provided by the interdisciplinary program for your back pain? *Responses: Very satisfied*; Rather satisfied*; Neither satisfied nor dissatisfied; Rather dissatisfied; Very dissatisfied (acceptability in *)*	Patients (both arms)	Proctor
	Narrative interviews	After 6-month primary outcome collection in the IG only	TFA; CFIR

GP: general practitioner, PT: physiotherapist; OT: occupational therapist; IG: intervention group; in grey, qualitative data collection.

Quantitative data will be collected through self-report questionnaires completed by healthcare professionals and patients in both groups. Qualitative data will be collected through focus groups (FG) (or semi-structured interviews if required) with GPs, physiotherapists, and occupational therapists after completion of patient recruitment [58,59]. Interviews will also be conducted with physiotherapists at the end of training and with patients in the intervention group after the 6-month primary outcome assessment to explore their experiences and acceptability of PRIME. Sampling will aim for diversity in professional roles, patient trajectories, and exposure to PRIME components. The final number of FG and interviews will be determined based on information power and availability of the participants [60]. FG and interview guides will be informed by implementation frameworks, as well as previous research and results from the pilot study whenever relevant [57,58].

### Sample size

2.8

The sample size was calculated based on the primary patient-level outcome (RMDQ) and the primary practitioner-level outcome (imaging prescription rate) [61]. Assuming 10 clusters per group with a mean of 20 patients per cluster, the study has 80.97% power to detect a between-group difference of 2.5 points on the RMDQ (SD = 6.0), using an intracluster correlation coefficient (ICC) of 0.05 and a two-sided significance level of 0.05 [62]. The ICC of 0.05 and the 20% allowance for loss to follow-up were informed by Darlow et al. (2019), who used the same assumptions in a comparable cluster-randomized primary care study evaluating the RMDQ. For back-related imaging, the same cluster structure provides 81.99% power to detect a 15% absolute reduction from a baseline imaging rate of 30%, assuming an ICC of 0.01 [35,63]. Allowing for a 20% dropout rate, a total of 500 patients will be recruited (25 patients per cluster).

Variation in cluster size was assessed using the coefficient of variation approach [64]. Given a minimum of 15 and a maximum of 35 patients per cluster (mean = 25), the coefficient was < 0.23 and considered negligible. Therefore, no adjustment was applied, and recruitment will stop once a cluster reaches 35 patients. No formal sample-size calculation was performed for cost-effectiveness due to limited Swiss data. We aim to recruit at least 100 general practitioners (approximately five patients per GP) and a minimum of 30 physiotherapists.

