### Randomization

2.9

The 20 clusters will be randomly allocated to the intervention or control group (1:1). Allocation concealment is ensured by the use of a computer-generated random sequence held by a blinded statistician, with cluster allocation unknown to recruiters prior to randomization. Randomization will be stratified by cluster size (small vs large, defined by the median number of GPs per cluster) to ensure balance between study arms.

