For patient-level primary outcome, an exploratory non-inferiority analysis will be performed using a margin of −2.5 points on the RMDQ, reflecting the possibility that the intervention may be acceptable if non-inferior and cost-saving. Pre-planned mediation analyses will examine the role of psychological factors in patient outcomes [70]. Different secondary analyses will be conducted, including the number of participants in each group that reach 30%, 50% and 70% of improvement on the RMDQ, as well as the number of participants reaching the patient acceptable symptom state (≤4 on RMDQ) [71]. All analyses will be performed using SAS (version 9.4) and Stata or R. Deviations from the statistical analysis plan will be documented and reported.

Given the three primary outcomes operating at distinct and complementary levels (system, practitioner, patient), findings will be interpreted jointly but are considered complementary rather than causally dependent. Each outcome is analyzed and reported independently, without formal alpha correction across levels. Discordant findings across levels are anticipated and theoretically meaningful: the three outcomes cover different domains serving different decision-making purposes, consistent with the GRADE Evidence to Decision framework [72].

Participants who withdraw or fail to complete baseline questionnaires will be considered screening failures and excluded from the trial. To ensure sufficient power at the primary endpoint, recruitment will continue until at least 200 patients per group have completed the 6-month assessment; consequently, total recruitment may exceed 500 participants. GP dropouts during the study period will not result in patient exclusion. Patient outcomes will be analyzed according to the cluster allocation at enrolment *(intention-to-treat principle)*.

For cost-effectiveness analyses, missing cost data will not be imputed; instead, they will be complemented where available with health insurance records. In case of discordance between data sources, patient questionnaire data will be considered primary and insurance data will be used for validation and to complement missing values. For outcomes other than costs, multiple imputation assuming data Missing at Random will be performed using SAS PROC MI for variables with more than 10% missing data, incorporating covariates, intervention group, and cluster information.

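### The printed 81.99% power for back-related imaging does not follow from its stated inputs: a fall from 30% to 15% has about 88–92% power

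*Protocol article*

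**What the plan says.** The protocol article bases its sample size on two of its three primary outcomes, RMDQ disability and back-related imaging (section 2.8, Sample size). The cluster structure is given first, for the RMDQ: "Assuming 10 clusters per group with a mean of 20 patients per cluster", with "a two-sided significance level of 0.05". The imaging sentence then carries that structure over and "provides 81.99% power to detect a 15% absolute reduction from a baseline imaging rate of 30%, assuming an ICC of 0.01".

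The significance level is not repeated for imaging, so two-sided 0.05 is the only level that the section offers. Section 2.12 (Statistical methods) confirms that it is not divided among the three primary outcomes: "Each outcome is analyzed and reported independently, without formal alpha correction across levels". Section 2.9 gives 1:1 allocation of 20 clusters.

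**The concern.** Everything needed to recompute the imaging power stands in or next to one sentence, and the recomputed power differs clearly from the printed one. Imaging is the primary practitioner-level outcome and one of only two outcomes with a power statement. A reader who checks the sentence cannot tell which part is wrong: the power, the direction of the 15 points, or the 30% baseline. The answer matters. If the rates are right, the trial is better powered for imaging than it claims. If the baseline is wrong, the planned effect is a different one.

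**Working it through.** **Inputs** (section 2.8 unless noted)

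- Clusters: 10 per arm, mean 20 patients, so n = 200 per arm; 1:1 allocation (section 2.9).
- ICC 0.01, so the design effect is 1 + (20 − 1) × 0.01 = 1.19 and the effective n is 200 / 1.19 = 168.1 per arm.
- Rates: 30% under usual care, 30% − 15 points = 15% under PRIME.
- Two-sided 0.05, critical z = 1.960.

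**Attempt to reproduce the printed 81.99% with 30% versus 15%**

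Unpooled normal formula, power = Φ(difference / SE − 1.960):

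- SE = √[(0.30 × 0.70 + 0.15 × 0.85) × 1.19 / 200] = √[(0.21 + 0.1275) × 1.19 / 200] = 0.04481
- 0.15 / 0.04481 = 3.347
- Power = Φ(3.347 − 1.960) = 0.9173

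Other standard choices with the same inputs:

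| Method, 30% vs 15% | Power |
|---|---|
| Unpooled z | 91.7% |
| Pooled z | 91.2% |
| Unpooled noncentral t, 18 df | 88.6% |
| Pooled noncentral t, 18 df | 87.6% |
| Continuity-corrected z | 88.9–89.3% |
| Arcsine | 91.6% |
| Log odds ratio | 90.0% |
| Beta-binomial simulation, cluster-level t-test | 89.0% |

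A cluster-size coefficient of variation of 0.23 changes little (91.5% by unpooled z, 88.3% by t). Using the 25 recruited patients per cluster instead of the 20 analysed raises the power further. To get 81.99% from 30% versus 15% by the unpooled z formula, the ICC would have to be about 0.032 instead of 0.01, or the cluster size about 14 instead of 20.

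**The same formula with the 15 points added**

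- SE = √[(0.21 + 0.45 × 0.55) × 1.19 / 200] = √[(0.21 + 0.2475) × 1.19 / 200] = 0.05217
- 0.15 / 0.05217 = 2.875
- Power = Φ(2.875 − 1.960) = 0.8199

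This agrees with the printed value in all four digits. Because the formula is symmetric in the two rates, 45% falling to 30% gives the same number. For these rates pooled z gives 81.4% and unpooled t on 18 df gives 77.6%.

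**Size of the discrepancy**

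87.6 − 81.99 = 5.6 points at the low end; 91.7 − 81.99 = 9.7 points at the high end.

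**Cross-check on the neighbouring figure**

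The same cluster structure with ICC 0.05 (design effect 1.95), SD 6.0 and a difference of 2.5 gives RMDQ power of 80.55%, 80.79% and 81.00% by a t-test on 18, 19 and 20 df, against the printed 80.97%. The cluster structure is therefore read correctly, and only the imaging figure is out of line.

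**The case against.** **Another significance level.** An alpha of 0.05/3 gives 81.96% by pooled z and 83.0% by unpooled z for 30% versus 15%. The first comes close, but it is not 81.99%, and section 2.12 rules out an alpha correction across the three outcomes. Using the control-arm variance in both arms with 18 df gives 81.0%; that is not a standard formula and does not match either.

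**The origin is not shown.** This stands. The article prints no formula or software input, and the four-digit match holds for the unpooled z formula only. The match makes 30% versus 45% the likely source but does not prove it.

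**The error does no harm.** For the effect as stated this also stands: the printed power is too low, not too high. A reader might infer that the trial is underpowered for imaging, since 45% to 30% gives 77.6% on 18 df. That needs both a 45% baseline, which appears nowhere in the article, and a t basis for the imaging calculation, which the article does not state. A plain sign slip with a correct 30% baseline explains the match equally well.

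**Different bases for the two power figures.** A reader might also fault the article for using a t-type calculation for the RMDQ and, apparently, a z-type one for imaging. No df from 18 to 20 gives exactly 80.97%, so the RMDQ method is not established. One outcome is continuous and the other binary, with different analysis models in section 2.12. Asking for one common basis is a preference, not the correction of an error.

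**Conclusion.** The printed imaging power is wrong for its stated inputs. A fall from 30% to 15% has about 88–92% power, depending on the formula, so 81.99% is about 6 to 10 points too low. This rests on the stated cluster structure and ICC, and on two-sided 0.05 applying to imaging as it does to the RMDQ. That the figure came from 30% versus 45% is very likely but remains an inference; only the sponsor can say whether the sign or the baseline went wrong.

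For the effect as stated, the target of 500 patients is unaffected, because the RMDQ, at about 81%, sets the limit. The documents do not support calling the trial underpowered for imaging. This is a planning figure that should be corrected, not a flaw in the design.

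**What to change.** Re-run the imaging calculation and restate the sentence in section 2.8 with both planning rates, the significance level, the formula and the power that matches them.

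- If 30% to 15% is the planned effect: give the power for the formula named, which will lie at about 88–92%.
- If 45% to 30% was meant: correct the baseline rate and give the power for those rates, 82.0% by unpooled z or 77.6% by t on 18 df, naming the one used.

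The cost is one re-run calculation and one corrected sentence, here and in any other trial document that repeats it. No change to enrolment follows for the effect as stated.

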### Randomization

2.9

The 20 clusters will be randomly allocated to the intervention or control group (1:1). Allocation concealment is ensured by the use of a computer-generated random sequence held by a blinded statistician, with cluster allocation unknown to recruiters prior to randomization. Randomization will be stratified by cluster size (small vs large, defined by the median number of GPs per cluster) to ensure balance between study arms.

### Blinding

2.10

Due to the nature of the intervention, investigators responsible for delivering the PRIME training ([name]) will be aware of GP cluster allocation but will not be involved in data collection, data management, or statistical analyses. In case of a serious adverse event or medical condition, the PI may contact participants while aware of allocation, but any decision regarding participant exclusion will be made by a blinded medical doctor.

Outcome data will be entered directly by patient participants via Research Electronic Data Capture (REDCap) [65]. Research staff contacting participants for questionnaire reminders will be blinded to group allocation. REDCap access for data collection staff is configured to exclude cluster and group identifiers. Reminder contacts follow standardized scripts that do not reference intervention components or care received, and patients are unaware of their group allocation. Staff conducting qualitative interviews will be aware of allocation, as interviews will be restricted to participants in the intervention group. Therefore, interviews will be conducted after completion of the 6-month primary outcome assessment.

GPs and physiotherapists will be aware of their allocation due to intervention delivery but will not be involved in data collection or analysis. Patients will remain unaware of their group allocation through limited disclosure and will be informed only that the study evaluates care pathways for LBP. Patients in the intervention group may possibly infer their allocation through receipt of PRIME components (e.g., patient education booklet). However, this is inherent to complex behavioral interventions and is acknowledged as a limitation.

Data cleaning and statistical analyses will be performed by a statistician blinded to group allocation. The analysis dataset will not include cluster or group identifiers, and results will be unblinded only after completion of analyses.

### Data collection and management

2.11

Patient- and practitioner-reported data will be collected and managed using REDCap and securely stored on Geneva University Hospital (HUG) servers protected by institutional firewalls. Data modifications will be fully traceable within REDCap. Identifiable information will be stored separately from coded study data in distinct REDCap projects.

Data not collected via REDCap (e.g. qualitative data and administrative cost data) will be stored on secure university servers. Access to all study data will be limited to authorised research team members using institutional access control and password protection. All study data will be coded automatically in REDCap.

### Statistical methods

2.12

Cost-effectiveness will be evaluated as the incremental cost-effectiveness ratio (ICER), expressed as net cost in CHF per quality-adjusted life-year (QALY) gained. QALYs will be derived from the EQ-5D-5L assessed at baseline and at 3, 6, and 12 months, using the French EQ-5D-5L value set [66], as there is currently no value set for Switzerland. QALYs will be estimated using the area-under-the-curve method over the 12-month follow-up, meaning that QALYs are calculated by multiplying the patients’ health state utility scores with the time spent in that health state.

Costs from the healthcare payer perspective will be estimated from self-reported healthcare utilization and, where available, health insurance data, applying current Swiss tariffs (TARDOC). The societal perspective will additionally include productivity losses due to absenteeism and presenteeism, assessed using the WPAI. Costs and QALYs will not be discounted given the one-year time horizon. Uncertainty will be assessed using non-parametric bootstrapping to estimate 95% confidence intervals for the ICER, and probabilistic sensitivity analyses will be conducted [67,68]. Cost-effectiveness will be explored across a range of willingness-to-pay thresholds.

Practitioner and patient-level outcomes will be analyzed according to the intention-to-treat principle by a blinded statistician. Primary and secondary continuous outcomes will be analyzed using linear mixed-effects models with random intercepts for clusters to account for the hierarchical structure of the data (patients nested within quality circles). Adjusted models will also be performed based on baseline variables (e.g. age, gender, socio-economic health determinants, RMDQ). Categorical outcomes (e.g. imaging prescription) will be analyzed using generalized linear mixed models [69].

For patient-level primary outcome, an exploratory non-inferiority analysis will be performed using a margin of −2.5 points on the RMDQ, reflecting the possibility that the intervention may be acceptable if non-inferior and cost-saving. Pre-planned mediation analyses will examine the role of psychological factors in patient outcomes [70]. Different secondary analyses will be conducted, including the number of participants in each group that reach 30%, 50% and 70% of improvement on the RMDQ, as well as the number of participants reaching the patient acceptable symptom state (≤4 on RMDQ) [71]. All analyses will be performed using SAS (version 9.4) and Stata or R. Deviations from the statistical analysis plan will be documented and reported.

Given the three primary outcomes operating at distinct and complementary levels (system, practitioner, patient), findings will be interpreted jointly but are considered complementary rather than causally dependent. Each outcome is analyzed and reported independently, without formal alpha correction across levels. Discordant findings across levels are anticipated and theoretically meaningful: the three outcomes cover different domains serving different decision-making purposes, consistent with the GRADE Evidence to Decision framework [72].

Participants who withdraw or fail to complete baseline questionnaires will be considered screening failures and excluded from the trial. To ensure sufficient power at the primary endpoint, recruitment will continue until at least 200 patients per group have completed the 6-month assessment; consequently, total recruitment may exceed 500 participants. GP dropouts during the study period will not result in patient exclusion. Patient outcomes will be analyzed according to the cluster allocation at enrolment *(intention-to-treat principle)*.

For cost-effectiveness analyses, missing cost data will not be imputed; instead, they will be complemented where available with health insurance records. In case of discordance between data sources, patient questionnaire data will be considered primary and insurance data will be used for validation and to complement missing values. For outcomes other than costs, multiple imputation assuming data Missing at Random will be performed using SAS PROC MI for variables with more than 10% missing data, incorporating covariates, intervention group, and cluster information.

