Several risks and limitations should be considered. First, patient recruitment is led by GPs, which may introduce selection bias despite mitigation strategies. Second, recruitment may also be challenging given GP workload, even though we included a high number of GPs in the study and developed recruitment strategies with a low time burden. If recruitment targets are not achieved, the recruitment period may be extended and additional eligible clusters may be recruited. If the final sample size remains below target, this will result in greater imprecision of the effect estimates and an increased risk of type II error, which will be acknowledged in the limitations. Third, the geographically limited setting increases the risk of contamination, particularly if patients in the control group consult trained physiotherapists. This will be monitored through patient questionnaires that will capture whether control-arm participants consulted a PRIME-trained physiotherapist. In such cases, sensitivity analyses will be conducted to assess the impact on primary outcomes. GP-level contamination is minimized by excluding GPs from the same practice who belong to different quality circles, and by restricting intervention materials (training content, digital tools, reminder emails) to intervention clusters only. The risk that control GPs will be passively exposed to intervention components in a meaningful way is low, and the risk that any exposure leads to important practice change to be even less [19]. Fourth, baseline data were collected after the initial GP consultation, which may limit evaluation of early consultation effects. Fifth, although LBP prevalence in primary care is not known to vary substantially by season, temporal factors such as GP availability during holiday periods or staggered training schedules could influence recruitment rates. Cluster-level recruitment monitoring will be conducted throughout the enrolment period. Finally, the effectiveness of complex behavioral interventions depends on fidelity and engagement, which may vary across clinicians, and co-interventions cannot be fully controlled. Accordingly, this trial primarily evaluates the effectiveness of interventions targeting healthcare professionals rather than individual clinical encounters.

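### The main RMDQ analysis reads as unadjusted, with baseline RMDQ only in additional models and the cluster-size stratum not named; this gives up precision and protection against imbalance

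*Protocol article*

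**What the plan says.** Section 2.12 of the protocol article analyses continuous outcomes with linear mixed models and a random intercept for each quality circle. No fixed effects are listed. The next sentence reads: "Adjusted models will also be performed based on baseline variables (e.g. age, gender, socio-economic health determinants, RMDQ". Categorical outcomes, including imaging, get generalized linear mixed models, again without named covariates.

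Section 2.9 states: "Randomization will be stratified by cluster size (small vs large, defined by the median number of GPs per cluster". Section 2.12 does not mention that factor.

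Section 2.8 bases power on an unadjusted standard deviation: "Assuming 10 clusters per group with a mean of 20 patients per cluster", a "between-group difference of 2.5 points on the RMDQ (SD = 6.0", and an "intracluster correlation coefficient (ICC) of 0.05 and a two-sided significance level of 0.05".

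Three further places matter:
- Sections 2.4.2 and 2.10: patients enter after cluster randomization, through GPs who know their allocation. The Discussion (section 3) accepts that this may introduce selection bias.
- Section 3 concedes that "baseline data were collected after the initial GP consultation".
- Section 2.6 assigns PSEQ-2, BSQ and Back-PAQ to the study of mechanisms. Table 2 uses Back-PAQ and FABQ at Baseline 2 as indirect measures of GP fidelity.

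**The concern.** Baseline score is usually a good predictor of the later score on the same scale, and the trial collects it from every patient it keeps, because patients without baseline questionnaires count as screening failures. Leaving it out of the main model discards precision already paid for.

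Two features of this design add weight. With only 20 randomized units, the arms can differ in baseline disability by chance. Recruitment by GPs who know their arm can also produce a difference that is not chance. An unadjusted main estimate carries part of either difference straight into the reported effect.

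The open covariate list carries a smaller hazard. Nothing in it rules out belief, fear or self-efficacy scores taken after the first consultation. Table 2 reads two such scores as signs of whether the GP delivered PRIME, so the protocol itself expects the intervention to move them. Adjusting the primary model for them would remove part of the effect being estimated.

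**Working it through.** **Inputs (section 2.8).** 10 clusters per arm, 20 analysed patients per cluster (200 per arm), difference 2.5, SD 6.0 (variance 36), ICC 0.05, two-sided 5% level.

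**The plan's own figure.**
- Design effect: 1 + (20 − 1) × 0.05 = 1.95.
- SE of the difference: √(2 × 36 × 1.95 / 200) = 0.838.
- Power from the noncentral t with 20 − 2 = 18 df: 80.6%. The plan says "the study has 80.97% power to detect" this difference, so the figure reproduces closely. A normal approximation would give 84.7%.
- Recruitment: 400 / (1 − 0.20) = 500, as stated.

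The stated power is therefore that of an unadjusted comparison with between-cluster degrees of freedom.

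**With baseline RMDQ in the model.** Let r be the correlation between baseline and 6-month RMDQ. The documents do not give it, so 0.3 to 0.6 is an assumption. Between-cluster variance is 0.05 × 36 = 1.8 and within-cluster variance is 0.95 × 36 = 34.2. Two cases bracket the gain:
- Variance falls at both levels: SE = 0.838 × √(1 − r²).
- Variance falls within clusters only: SE = √(2 × [1.8 + 34.2 × (1 − r²)/20] / 10).

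Power uses 17 df, to allow for one stratum term.

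| r | SE, both levels | Power | SE, within only | Power |
|---|---|---|---|---|
| 0.3 | 0.799 | 83.8% | 0.819 | 82.0% |
| 0.5 | 0.726 | 90.1% | 0.785 | 85.1% |
| 0.6 | 0.670 | 94.0% | 0.761 | 87.2% |

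**The stratum alone (17 df).** If cluster size explains 0%, 10% or 25% of between-cluster variance (assumed), power with the stratum is 80.3%, 82.3% or 85.3%. If it is left out, the estimate is not biased. The test becomes slightly conservative when the stratum is prognostic: approximate type I error 0.046 at 10% and 0.038 at 25%.

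**Chance imbalance.** Assume that baseline RMDQ has the SD and ICC that the plan gives the outcome. The arm difference at baseline then also has SE 0.838, and a difference of 1 point or more has probability 2 × [1 − Φ(1/0.838)] = 23%. With equal SDs the regression slope is about r, so a 1-point imbalance shifts the unadjusted estimate by about 0.3 to 0.6 points, against a target of 2.5.

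**The possible loss.** Suppose the first PRIME consultation has already lowered baseline RMDQ by δ points. The adjusted effect then shrinks by about r × δ. At r = 0.5, the effect giving 80.6% power on 17 df is 2.173 (SE 0.726) or 2.351 (SE 0.785). The power gain is therefore cancelled at δ = (2.5 − 2.173)/0.5 = 0.65 or (2.5 − 2.351)/0.5 = 0.30 points.

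**The case against.** The strongest reply is that this is a condensed article. Section 2.12 refers to a statistical analysis plan that is not shown, and covariate lists, stratum terms and degrees-of-freedom methods normally sit there. That disposes of any complaint about mere silence. It does not dispose of the order the article does state: the mixed model comes first, and adjusted models are run as well.

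Second, baseline follows the first consultation with a trained GP, so adjusting for it may condition on something PRIME has already touched. This stands as a real cost. It is a reason to keep the unadjusted model as a sensitivity analysis and to report both.

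Third, the trial was sized without adjustment and meets its target, so the gain is above target and depends on an assumed r. At r = 0.3 it is only 1 to 3 percentage points. This also stands.

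A reader might infer more than the text supports:
- That the stratum is excluded. It is only not named; the model's fixed effects are not listed and the covariate examples are open.
- That the test has inflated type I error with 20 clusters. No z-based test is specified, and the stated power fits 18 df.
- That the plan intends to adjust for psychological scores. None is among the examples, and section 2.12 assigns psychological factors to mediation analyses.
- That RMDQ is taken at the wrong baseline visit. The schedule is in Supplementary Material S4, which is not shown.
- That the team could pick the model after seeing the results. The article names no model as primary, but section 2.10 provides for a blinded statistician and unblinding only after the analyses.

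**Conclusion.** The point holds as a matter of efficiency and robustness, not validity. The unadjusted analysis is valid and has about 80% power on the plan's inputs. Placing baseline RMDQ in additional models forgoes a gain to about 82% to 94% power at the same sample size, given r between 0.3 and 0.6, an undiminished 2.5-point effect and the plan's SD and ICC. It also leaves chance or recruitment-related imbalance in baseline disability uncorrected in the main estimate; the additional models would show it, but they are not the headline result. For the stratum, the documents establish neither exclusion nor a definite loss. Naming it costs almost nothing and matches the analysis to the randomization. The change is worth making, but the trial does not fail without it.

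**What to change.** State one primary model for RMDQ at 6 months: a linear mixed model with treatment, baseline RMDQ, the cluster-size stratum, a short closed list such as age and gender, and a random cluster intercept. Include the stratum in the generalized linear mixed model for imaging. Keep the unadjusted model as a sensitivity analysis, and report it beside the primary result so that any attenuation through post-consultation baseline can be seen. State that Baseline 2 belief, fear and self-efficacy measures do not enter the primary model and belong to the mediation and fidelity analyses.

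The cost is wording in the protocol and the statistical analysis plan, settled before unblinding. It needs no further patients or data. Statistically it costs one of 18 between-cluster degrees of freedom (power 80.3% instead of 80.6% if nothing added is prognostic) and the possible attenuation shown above. If the unseen analysis plan already specifies this model, only the article's wording needs aligning.
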